### Safety evaluation

Adverse events (AEs), including AEs related to acupuncture (broken needle, local hematoma, infection, abscess, and others), AEs related to postacupuncture (nausea, vomiting, palpitations, dizziness, headache, insomnia, or any other symptoms after acupuncture treatment), and AEs unrelated to treatment will be recorded. For safety assessment, details of all AEs will be recorded by a research assistant in the case report form. Any serious adverse events will be reported within 24 h to the Ethics Approval Committee of the Guang’anmen Hospital of China Academy of Chinese Medical Sciences. The Department of Acupuncture of the Guang’anmen Hospital of China will provide insurance coverage to compensate for any injuries related to the interventions during this study.

### Sample size and statistical analysis

The sample size of this trial was calculated on the basis of primary outcome, which is the change from baseline in the Skindex-16 scale score at the end of week 4. In our unpublished pilot trial, the mean (± standard deviation) reductions in the Skindex-16 scale score after 4-week treatment in the acupuncture and sham acupuncture groups were 12.50 ± 19.09 and 0.40 ± 21.12, respectively. Assuming an alpha risk of 5% and a beta risk of 20%, a sample size of 100 (50 participants in each group) was calculated, considering a 20% dropout rate.

The data will be analyzed using IBM SPSS Statistics version 20.0 software (IBM Corp, Armonk, NY, USA) according to the intention-to-treat principle. Normally distributed continuous variables will be reported as mean ± standard deviation or 95% confidence intervals; non-normally distributed continuous variables will be reported as median (interquartile range). Categorical variables will be presented as frequency (percent). For data pertaining to dropouts, the actual observational value of the last observation will be used for statistical analysis. Between-group differences with respect to normally distributed continuous variables will be assessed using analysis of variance, and those with respect to non-normally distributed continuous variables will be assessed using nonparametric tests for the primary outcome and the secondary outcomes. Data pertaining to the participants’ expectations of acupuncture and the safety evaluation will be analyzed using the chi-square test or Fisher’s exact test. For the blinding assessment, the percentage of participants choosing traditional acupuncture will be assessed using the chi-square test. All *P* values will be two-tailed; *P* < 0.05 will be considered indicative of statistical significance.

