Several trials have indicated that acupuncture may alleviate the skin lesions and improve the QoL of patients with AV [11–15]. However, these trials were affected by potential bias due to small sample sizes, nonplacebo/sham/waiting list control, or use of self-defined outcome measures; thus, they did not provide robust evidence of the efficacy of acupuncture in patients with AV. Therefore, we conducted a pilot trial (unpublished) from April 2017 to March 2018 in which 42 patients with moderate or severe AV were randomly allocated to an acupuncture group (*n* = 21) or a sham acupuncture group (*n* = 21). After a 4-week treatment, the number of inflammatory lesions in the acupuncture group (*n* = 21) was 35.62 ± 15.51, with a reduction of 6.62 ± 15.42 from baseline. The number of inflammatory lesions in the sham acupuncture group (*n* = 21) was 30.05 ± 21.16, with a reduction of 15.10 ± 20.13 from the baseline. The difference between the two groups was 8.48 ± 7.74, and there was no significant between-group difference with the *p* = 0.137 due to *p* > 0.05 was considered nonsignificant. These findings contradict the results of previous trials [11–14], and authors of a systematic review of AV also reported that there was no difference between acupuncture and the waiting list for reducing the number of inflammatory lesions [16]. Unlike drugs, which act directly on the pathogen, acupuncture restores normal functions through motivating or inducing the inherent regulatory system [17]. Therefore, acupuncture may relieve other symptoms of AV (itch or pain) [18, 19] and improve the QoL [11]. The Skindex-16 scale is a sensitive and specific tool for assessing the symptoms and QoL of patients with AV, and it includes seven questions related to the symptoms (itch or pain) and characteristics (skin lesions) of AV [20, 21]. Following the 4-week treatment, the total score on the Skindex-16 scale for acupuncture (*n* = 21) was 19.89 ± 15.40, with a reduction of 12.50 ± 19.09 from the baseline. The total score on the Skindex-16 scale for sham acupuncture (*n* = 21) was 30.43 ± 19.39, with a reduction of 0.40 ± 21.12 from the baseline. The difference between the two groups was − 12.9 ± 11, and there was a significant between-group difference in this instance with the *p* = 0.044 due to *p* < 0.05 was considered statistically significant. Therefore, the results of our pilot study indicated that acupuncture may help to relieve total symptoms and improve the QoL of patients with moderate or severe AV. So far, there are two systematic reviews that recommend using the measure of QoL for evaluating the effect of acupuncture on AV [10, 16], but no clinical trials have been conducted that use the measure of QoL to evaluate the effect of acupuncture on the symptoms and the QoL of patients with AV. Therefore, we intend to use the Skindex-16 scale as a primary outcome measure in our planned study to evaluate the effect of acupuncture compared with sham acupuncture on the symptoms and QoL of patients with moderate or severe AV.

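### The pilot figures behind the sample size disagree: the printed reductions differ by 12.1, but the reported difference, its p-value and N = 100 fit 12.9

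*Protocol article*

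**What the plan says.** In the protocol article, the section on sample size and statistical analysis gives the pilot mean reductions in Skindex-16 after 4 weeks: "acupuncture and sham acupuncture groups were 12.50 ± 19.09 and 0.40 ± 21.12, respectively". The error rates are given as "Assuming an alpha risk of 5% and a beta risk of 20" per cent, and the same section says of the P "values will be two-tailed". From these it concludes that "a sample size of 100 (50 participants in each group) was calculated, considering a 20% dropout rate". It names neither the between-group difference nor the SD that entered the calculation.

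The Background reports the same pilot, with 21 patients per arm. It too describes the sham change as a fall: "with a reduction of 0.40 ± 21.12 from the baseline". It then gives the between-group difference, printed with a minus sign, as "12.9 ± 11, and there was a significant between-group difference in this instance", with p = 0.044.

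**The concern.** Both sections describe the sham change as a reduction of 0.40, so the difference in reductions should be 12.50 − 0.40 = 12.1. The reported 12.9 is 12.50 + 0.40 and can arise only if the sham score rose by 0.40. At least one printed pilot statement is therefore wrong.

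Subtracting reductions is also the convention of that paragraph. For inflammatory lesions, the reported difference of 8.48 is 15.10 − 6.62, one reduction less the other.

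Two things turn on the sign:

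- **The sample size.** It is said to rest on these inputs, and 12.1 and 12.9 do not lead to the same number.
- **The pilot result.** The Background calls the Skindex-16 difference significant and uses it to argue that acupuncture may help, before choosing Skindex-16 as the primary outcome. At 12.1 the pilot does not reach the article's own 0.05 threshold.

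**Working it through.** **Inputs.** From the sample size section: SDs of 19.09 and 21.12, alpha 5% (two-sided, from the statement on P values), power 80%, dropout 20%. From the randomization section: 1:1 allocation. From the Background: 21 pilot patients per arm and a reported difference of 12.9. The planned primary test, analysis of variance on the change with two groups, is equivalent to a t-test.

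**Variance.** 19.09² + 21.12² = 364.43 + 446.05 = 810.48; pooled SD = √(810.48/2) = 20.13.

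**Patients per arm.** n = (1.960 + 0.842)² × 810.48 / d², where (1.960 + 0.842)² is about 7.85. The exact t solution adds about one patient. Dropout is applied as n/(1 − 0.2).

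| | d = 12.9 (reported difference) | d = 12.1 (printed reductions) |
|---|---|---|
| n per arm, normal | 38.2, so 39 | 43.4, so 44 |
| n per arm, t | 39.2, so 40 | 44.4, so 45 |
| per arm after dropout | 49 (normal), 50 (t) | 55 (normal), 57 (t) |
| total | 98 (normal), **100** (t) | **110** (normal), **114** (t) |
| power at 40 per arm, t | 80.8% | 75.6% |
| power at 40 per arm, normal | 81.7% | 76.7% |

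The plan's figure is reproduced exactly with 12.9 and the t-test: 40/0.8 = 50 per arm. Inflating by 1.2 instead of dividing by 0.8 does not rescue 12.1: it gives 53 or 54 per arm, 106 to 108 in total.

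**Power at 40 per arm (50 less 20%).** The standard error of the difference is 20.13 × √(2/40) = 4.50. The noncentrality is 12.1/4.50 = 2.69 or 12.9/4.50 = 2.87, on 78 degrees of freedom.

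**Pilot p-value.** SE = √(810.48/21) = 6.21, on 40 degrees of freedom.

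- d = 12.9: t = 12.9/6.21 = 2.08, p = 0.044, as printed.
- d = 12.1: t = 12.1/6.21 = 1.95, p = 0.058.

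The 11 printed after the 12.9 is not labelled. It matches neither this SE (6.21) nor the half-width of a 95% interval (12.56), so it does not help to settle the sign.

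**The case against.** The strongest reply is that the trial may be sized correctly. The reported difference, the p-value and N = 100 all agree with 12.9; only the description of the sham change disagrees. A lost minus sign, or loose use of the word reduction for a rise of 0.40, would explain everything. This stands. It makes the wrong sham direction the likelier error, though it does not remove the contradiction, because the wording appears in both sections.

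Three further points limit what can be claimed.

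- **N = 100 is not uniquely tied to 12.9.** A difference of 12.1 with the acupuncture SD alone gives 2 × 19.09² × 7.85 / 12.1² = 39.07, so 40 per arm and 50 after dropout (normal approximation). Ignoring the larger sham SD is not standard, but the article does not say which SD was used.
- **The 76% depends on 40 evaluable patients per arm at week 4.** The article does not say when the 20% drop out, and follow-up runs to week 28. The plan also carries the last observation forward, so 50 per arm could enter the analysis; at 12.1 that gives about 85% if effect and SD are unchanged. That is an upper bound: Table 1 schedules no Skindex-16 between baseline and week 4, so an early dropout would carry forward baseline, a change of zero.
- **The stakes are modest.** The gap of 0.8 points is small beside the pilot SE of 6.21, and both differences exceed the stated minimal important difference of 10. Pilot significance is not the only reason given for Skindex-16: the Background also cites possible relief of itch and pain, and two systematic reviews recommending quality-of-life measures.

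These points narrow the consequence. They do not make the printed inputs yield the printed N under the standard calculation.

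**Conclusion.** The inconsistency is real and needs correcting. Under the standard two-sided calculation with both SDs, 100 patients follow from a difference of 12.9 and not from the 12.1 implied by the printed reductions, which calls for 110 to 114.

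A reader might infer that the trial has 76% power instead of 80%, or that the pilot was not significant. The document supports neither as a flat statement. Both hold only if sham truly fell by 0.40, and the 76% further assumes 40 evaluable patients per arm at week 4. If sham worsened by 0.40, the likelier reading, power is about 81% on the same assumption, and both N = 100 and p = 0.044 stand. Nor can one say that only 12.9 could have produced 100, since the SD used is not stated.

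**What to change.** Check the direction of the sham change in the pilot data, make the Background and the sample size section agree, and state the difference and SD used in the calculation.

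- **If sham worsened by 0.40:** describe the sham change as an increase in both sections and state that the sample size uses 12.9. N = 100 stands.
- **If sham fell by 0.40:** correct the difference to 12.1 and the pilot p-value to 0.058, withdraw the statement that the pilot difference was significant, and restate the power at N = 100 with 20% dropout as about 76%.

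The cost is a look-up and corrected wording, with possibly a slightly less favourable power figure. No extra patients are needed unless the sponsor finds that 12.1 is right and wishes to keep 80%, which would take 110 to 114. The article reports no recruitment at the time of writing, so the correction comes cheaply.

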### Outcome measures

The primary outcome will be the change in the total score of the Skindex-16 scale from baseline at the end of 4-week treatment. The Skindex-16 scale is a brief, skin-related QoL scale with satisfactory reliability and validity [20, 21]. It is used to evaluate the efficacy of acupuncture in improving the QoL of patients with AV [20, 21]. The scale includes a total of 16 items that are categorized into three domains: the symptoms of participants with AV, the emotions of participants with AV, and function of participants with AV [20, 21]. The Skindex-16 scale score ranges from 0 (best) to 100 (worst), with a minimal clinically important difference (MCID) as 10 [20, 21].

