### Secondary outcomes

The change from baseline in the Skindex-16 scale total score at weeks 16 and 28The change from baseline in the Skindex-16 subscale (the symptoms of participants with AV, the emotions of participants with AV, and functioning of participants with AV) scores at weeks 4, 16, and 28The change from baseline in the Dermatology Life Quality Index (DLQI) [29] scale total score at weeks 16 and 28. The DLQI scale is a tool used to assess the health-related QoL of patients with skin diseases. It has a total of ten items. The total score of DLQI ranges from 0 (best) to 30 (worst), with 4 as the MCID in inflammatory skin diseases [30].The change from baseline in the total lesion (inflammatory and noninflammatory lesions) count (TLC) [31, 32] at weeks 4, 16, and 28The change from baseline in the inflammatory lesion count (ILC) [26] at weeks 4, 16, and 28. Inflammatory lesions include inflammatory papules, pustules, and cysts. Noninflammatory lesions include blackhead and whitehead comedones. The lesions are assessed on the forehead, cheeks, nose, and chin. The inflammatory and noninflammatory lesions are counted from the pictures of the face obtained by a dermatologist using a digital camera.The change from baseline in the degree of itch assessed using the Itch Assessment with Visual Analogue Scale (IVAS) [32] at weeks 4, 16, and 28The change from baseline in the severity of pain assessed by visual analogue scale (PVAS) [33] at weeks 4, 16, and 28The participants’ expectations of acupuncture will be assessed at baseline using the following two questions: “Do you think acupuncture will be effective for treating the illness?” and “Do you think acupuncture will be effective for relieving the related symptoms of AV?” The response options will be “yes,” “no,” or “unclear.”

The details of the evaluation of outcomes are shown in Table 1.

**Table 1 Tab1:** Time points for assessment of outcomes

Outcome measures	Enrollment and allocation	Treatment				Follow-up	
	Baseline	Week 1	Week 2	Week 3	Week 4	Week 16	Week 28
Skindex-16 total score	X				X	X	X
Skindex-16 subscales score	X				X	X	X
DLQI total score	X				X	X	X
TLC	X				X	X	X
ILC	X				X	X	X
IVAS score	X				X	X	X
PVAS score	X				X	X	X
Blinding assessment					X		
Expectation	X						
Safety assessment		X	X	X	X		

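### Carrying the last observation forward gives anyone lost before week 4 a primary change of exactly zero, which biases the estimated effect although it costs little power

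*Protocol article*

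**What the plan says.** Under Outcome measures, the endpoint is defined thus: "The primary outcome will be the change in the total score of the Skindex-16 scale from baseline at the end of 4-week treatment". Table 1, "Time points for assessment of outcomes", marks the row "Skindex-16 total score" at baseline, week 4, week 16 and week 28, and leaves weeks 1, 2 and 3 blank. The rows for DLQI, TLC, ILC, IVAS and PVAS have the same pattern.

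Under Sample size and statistical analysis, the data are analysed "according to the intention-to-treat principle". The missing-data rule is: "For data pertaining to dropouts, the actual observational value of the last observation will be used for statistical analysis". The test is given as "Between-group differences with respect to normally distributed continuous variables will be assessed using analysis of variance", with nonparametric tests otherwise, and P "values will be two-tailed". On size: "Assuming an alpha risk of 5% and a beta risk of 20%, a sample size of 100 (50 participants in each group) was calculated", allowing for 20% dropout. The article does not say when in the 28 weeks that dropout is expected, and it names no other missing-data analysis.

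**The concern.** Carrying a value forward needs an earlier post-baseline value. The primary outcome has none, so for early dropouts the rule becomes baseline carried forward, with a change of exactly 0. That is a strong assumption about people whose week-4 state is unknown, and single imputation treats the assigned value as if it had been measured.

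What is at stake is the primary estimate. If the arms lose the same proportion, the treatment difference is diluted by that proportion. If they lose different proportions, the arm with more dropout is pulled further towards no change, so a difference can be hidden, enlarged or created. For those who leave after week 4, the rule assumes that the last observed score persists to weeks 16 and 28, so durability is partly built in by the imputation.

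**Working it through.** **Inputs.** Pilot reductions are 12.50 (SD 19.09) for acupuncture and 0.40 (SD 21.12) for sham (Background; Sample size and statistical analysis). Their difference is 12.50 − 0.40 = 12.1. The Background section reports the pilot difference as 12.9 in absolute value, so both are carried through; 12.9 corresponds to a sham mean of −0.40. Pooled SD = √((19.09² + 21.12²)/2) = 20.13. Alpha is two-sided 5%, power 80%, dropout 20%, with 50 per arm.

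**The plan's own figure.** With difference 12.9 and SD 20.13, a two-sample t-test needs 40 per arm; 40/(1 − 0.2) = 50 per arm, total 100. This reproduces the plan. With 12.1 and the same SD, the t-test needs 45 per arm, then 57 after inflation, which does not. The pilot's stated p = 0.044 also fits 12.9 (12.1 gives p = 0.058), so the two sections need reconciling. That is a separate matter from the imputation rule.

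**Effect of the rule.** If a fraction q of an arm with mean change μ and standard deviation SD is set to 0:

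- mean = (1 − q)μ
- variance = (1 − q)SD² + q(1 − q)μ²

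*Equal loss of 20%, difference 12.1.* Expected difference = 0.8 × 12.1 = 9.68. Acupuncture SD = √(0.8 × 19.09² + 0.16 × 12.5²) = 17.8; sham SD = √(0.8 × 21.12² + 0.16 × 0.4²) = 18.9; pooled 18.35. The SD falls as well as the mean, and all 50 per arm stay in the analysis.

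The last two columns give t-test power with carried-forward values (50 per arm) and with observed cases only:

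| Loss before week 4 (acupuncture / sham) | True difference | Expected difference under the rule | Power, rule | Power, observed cases |
|---|---|---|---|---|
| 10% / 10% (assumed) | 12.1 | 10.89 | 79.9% | 80.5% |
| 10% / 10% (assumed) | 12.9 | 11.61 | 84.6% | 85.2% |
| 20% / 20% (upper case) | 12.1 | 9.68 | 74.3% | 75.6% |
| 20% / 20% (upper case) | 12.9 | 10.32 | 79.5% | 80.8% |
| 30% / 10% (assumed) | 12.1 | 8.39 | 60.9% | 75.0% |
| 30% / 10% (assumed) | 12.9 | 9.11 | 68.1% | 80.2% |
| 10% / 30% (assumed) | 12.1 | 10.97 | 85.1% | 75.0% |
| 10% / 30% (assumed) | 12.9 | 11.53 | 88.4% | 80.2% |

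Unequal rows follow the same formula, for example 0.7 × 12.5 − 0.9 × 0.4 = 8.39.

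**No true difference.** Suppose both arms improve by the same amount μ. The false difference is then μ × (difference in dropout). Type I error was simulated with t-tests, 50 per arm, SD 20.13:

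- μ = 12.5 (assumed), equal 20% loss: no false difference, type I error not inflated (5% or slightly below).
- μ = 12.5, 15% v 25%: false difference 12.5 × 0.10 = 1.25; type I error about 6%.
- μ = 12.5, 10% v 30%: false difference 12.5 × 0.20 = 2.5; type I error about 10%.
- μ = 0.4 (the pilot sham mean), 10% v 30%: false difference 0.4 × 0.20 = 0.08; type I error about 5%.

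**The case against.** A reader might infer that the rule also consumes the planned power, since the sample size treats dropouts as lost while the analysis keeps them in at zero. The figures do not support that. At equal 20% loss the rule costs 1.3 points against observed cases, because the imputed zeros shrink the SD and keep 50 per arm. The power of about 74% at 12.1 comes from the smaller pilot difference, not from the rule; at 12.9, which reproduces the sample size, power stays at about 80%.

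Three further limits stand. First, 20% before week 4 is an upper case: the article gives no timing for dropout, follow-up runs to week 28, and losses after week 4 do not touch the primary outcome. An expected estimate below the stated MCID of 10 needs both that upper case and 12.1, and the protocol does not use the MCID as a success threshold. Second, the 10% type I error needs two assumptions together: 10% v 30% dropout, which nothing in the article suggests, and a 12.5-point improvement in both arms, well above the pilot sham mean of 0.40. Third, with equal dropout the rule pulls towards no effect, which is conservative for a superiority trial.

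For week 28, a false difference of 0.2 × 12.1 = 2.4 points could be constructed, but only if the effect has vanished and the whole 20% leaves after week 4. That cannot hold together with 20% lost before week 4.

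It is also fair that a mixed model gains little for participants with only a baseline score and rests on missing at random. That is a reason to add a sensitivity analysis. It does not justify zero change as the main assumption. Nor is this a detail left to an unseen analysis plan, because the article states the rule.

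**Conclusion.** The point holds as a bias problem in a stated analysis rule. Anyone lost before week 4 is analysed with a primary change of 0, and the same applies to DLQI, TLC, ILC, IVAS and PVAS. With equal loss the expected difference falls in proportion to dropout: by a tenth at an assumed 10%, and by a fifth at 20% if all planned dropout comes early. Power and type I error are then essentially unaffected.

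With unequal loss the direction depends on which arm loses more. Heavier loss under acupuncture (30% v 10%, assumed) lowers power to about 61% or 68%, and the reverse split raises it to about 85% or 88%. A material false-positive risk arises only if dropout is unequal and both arms improve substantially. These sizes rest on the pilot means and SDs and on dropout splits that the article does not give. Severity: should be fixed. It affects the primary estimate, but the serious consequences need conditions that the article does not assume.

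**What to change.** Replace carried-forward values as the main analysis with one that does not impute zero change. Two suitable choices are:

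- a mixed model for repeated measures using Skindex-16 at baseline and weeks 4, 16 and 28, with treatment-by-visit terms and the week-4 contrast as primary; or
- baseline-adjusted ANCOVA with multiple imputation by arm.

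Keep the carried-forward analysis as a sensitivity analysis. Add a delta-adjusted one, because the new main analysis assumes data missing at random. Apply the same to the other continuous outcomes.

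The cost is analysis wording and modest programming, with no extra visits or participants. The article's trial status reports no recruitment at the time of writing, so the change can be made before any outcome data are seen.

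### The primary analysis of change from baseline has no baseline covariate; it is valid, but ANCOVA on the baseline score already collected would be more precise at almost no cost

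*Protocol article*

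**What the plan says.** Under Outcome measures, the primary endpoint is a change score: "The primary outcome will be the change in the total score of the Skindex-16 scale from baseline at the end of 4-week treatment". Under Sample size and statistical analysis, the test is named: "Between-group differences with respect to normally distributed continuous variables will be assessed using analysis of variance". If the data are not normal, differences "will be assessed using nonparametric tests for the primary outcome and the secondary outcomes". No covariate or other baseline adjustment appears, and analysis of covariance is not mentioned anywhere in the article. The sample size is built on the change scores, with pilot reductions that "were 12.50 ± 19.09 and 0.40 ± 21.12, respectively".

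The Background section also gives the pilot week-4 scores. The acupuncture arm "was 19.89 ± 15.40, with a reduction of 12.50 ± 19.09 from the baseline"; the sham arm "was 30.43 ± 19.39, with a reduction of 0.40 ± 21.12 from the baseline". Table 1 shows that Skindex-16 and every other continuous outcome are measured at baseline. Dropouts are to be analysed with their last observed value.

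**The concern.** A change score gives the baseline a fixed weight of one. That is efficient only when baseline and follow-up are closely correlated. When the change is more variable than the follow-up score itself, as in both pilot arms, the correlation is weak and the subtraction adds noise. ANCOVA estimates the weight from the data. It also removes the part of any chance baseline difference that would otherwise enter the estimate through regression to the mean.

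At stake is precision in the one analysis on which the trial is sized. The authors themselves call the sample relatively small. The baseline score is collected in any case.

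**Working it through.** **Inputs.** From Background: SD of change 19.09 (acupuncture) and 21.12 (sham); SD at week 4 15.40 and 19.39; 21 patients per arm. From Sample size and statistical analysis: two-sided 5%, 80% power, 50 per arm, 20% dropout. The baseline SD is not given, so a range of 14 to 22 is assumed.

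**1. The plan's own figure.**
- Pooled SD of change = √[(19.09² + 21.12²)/2] = √405.2 = 20.13.
- With a difference of 12.9, the t-based calculation gives 40 per arm. Then 40/0.8 = 50 per arm, total 100, which matches the plan.
- With 12.50 − 0.40 = 12.1, it gives 45 per arm, then 57 after dropout, total 114.
- The stated N therefore corresponds to a difference of 12.9.

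**2. Change against week-4 score.**
- Pooled week-4 variance = (15.40² + 19.39²)/2 = 306.6, SD 17.51.
- Ratio 306.6/405.2 = 0.757, so the week-4 variance is 24.3% lower.
- By arm: 1 − (15.40/19.09)² = 35% (acupuncture); 1 − (19.39/21.12)² = 16% (sham).

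**3. ANCOVA among completers.**
- Residual variance = week-4 variance × (1 − ρ²), which cannot exceed 306.6. On the pilot point estimates the reduction is therefore 24% or more.
- With baseline SD s, ρ = (s² + 306.6 − 405.2)/(2 × s × 17.51).

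| Assumed baseline SD | ρ | Residual variance | Reduction against 405.2 |
|---|---|---|---|
| 14 | 0.20 | 294.5 | 27% |
| 17.51 | 0.34 | 271.3 | 33% |
| 22 | 0.50 | 229.9 | 43% |

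**4. ANCOVA under the last-observation rule.** During treatment, Skindex-16 is measured only at baseline and week 4. A patient lost before week 4 therefore enters with a change of zero. Assume that 20% are lost this way, that completers have the pilot SDs, and that dropouts have the same baseline distribution.
- Variance of change = 0.8 × 405.2 + 0.8 × 0.2 × (12.50² + 0.40²)/2 = 324.2 + 12.5 = 336.7.
- Covariance of baseline with change = 0.8 × [(s² + 306.6 − 405.2)/2 − s²].
- Variance removed by ANCOVA = that covariance squared, divided by s².
- s = 14: covariance −117.9, removed 70.9, reduction 70.9/336.7 = 21%.
- s = 22: covariance −233.1, removed 112.2, reduction 112.2/336.7 = 33%.

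**5. Power (two-sided t test, 40 evaluable per arm).** The last column uses SD 17.51, the least favourable ANCOVA case on the pilot estimates.

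| Difference | Change score (SD 20.13) | ANCOVA, at least |
|---|---|---|
| 12.1 | 76% | 86% |
| 12.9 | 81% | 90% |

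Under the assumptions of step 4, all 50 per arm are analysed and the effect is diluted to 0.8 × 12.1 = 9.68. Power then goes from about 74% to between 84% and 89% for s from 14 to 22.

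**6. Uncertainty and cost.** Simulating pilots of 21 per arm under normality, with assumed baseline SD 14 to 20, the 95% range for the completer ANCOVA reduction starts at 7% to 15% and ends at 52% to 61%. One covariate costs one degree of freedom, about 1% of the variance at 80 to 100 patients.

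**The case against.** The strongest reply is that nothing here is wrong. Analysis of variance on change is valid in a randomised trial, holds its type I error, matches the declared endpoint and uses the same SDs as the sample size. That stands: the point concerns efficiency only.

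A reader might take 24% as a guaranteed minimum. The documents do not support that. It is a point estimate from 21 patients per arm, it is only 16% in the sham arm, and it describes completers. Under the plan's own last-observation rule the figure can fall to about 21%. What does not depend on the pilot is the direction: apart from one degree of freedom, ANCOVA is not less precise than the change-score analysis.

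A reader might also infer that the planned test leaves the trial short of power and that adjustment rescues it. That holds only at 12.1. Background states "The difference between the two groups was − 12.9 ± 11". Its p value of 0.044 fits 12.9: the standard error is 20.13 × √(2/21) = 6.21, so t = 2.08. At 12.9 the change-score test with 40 per arm has 81% power. Which sign the sham change carries is a separate matter to be reconciled.

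Nor do the pilot baselines show troublesome imbalance. They are 12.50 + 19.89 = 32.39 against 30.83 or 30.03, a gap of 1.6 to 2.4 points. The standard error is about 17.51 × √(2/21) = 5.4 if the baseline SD equals the week-4 SD.

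Finally, the article is condensed, and its lack of adjustment is inferred from the absence of any covariate. A fuller plan might name one. But the test is stated here for the primary outcome, so this is a choice on the page and not a gap.

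**Conclusion.** The planned test is sound but gives up precision that the pilot data suggest is worth having. Among completers, the pilot point estimates imply a variance reduction of about 24% or more. With last observations carried forward and 20% dropout before week 4, it is about 21% to 33% for a baseline SD of 14 to 22. The dropout timing and the baseline SD are assumptions, and the pilot is small, so the size is uncertain while the direction is not. The gain applies whether the design difference is 12.1 or 12.9. This is a free improvement: it corrects no error or bias, and no power shortfall is claimed.

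**What to change.** Where the parametric analysis applies, make the primary analysis an ANCOVA of the week-4 Skindex-16 total on arm, with baseline Skindex-16 as covariate, and report the adjusted mean difference with its 95% CI. Using the change as the response gives the same treatment contrast, so the declared endpoint can stay. Use the same form, each with its own baseline, for the Skindex-16 subscales, DLQI, the two lesion counts and the itch and pain scales.

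The cost is a sentence in the analysis section and one degree of freedom per model. It needs no new data and no more patients. The article's Trial status section reports no current recruitment. If enrolment has still not begun, the change can be made before any patient is randomised.
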